**4. STUDY POPULATION**

**4.1 Population**

Healthy Caucasian men (from the student population of Wageningen University), age between 18 and 30 years. Women are excluded from the study population since macrovascular EF, microvascular EF and arterial stiffness outcomes show variation during the menstrual cycle 15-17.

**4.2 Screening visit**

Before the screening, volunteers have to give their written informed consent. A general and medical questionnaire will be filled out, containing questions concerning our exclusion criteria. Fasting blood and urine samples will be collected and the following parameters will be determined for all volunteers:

• Fasting blood glucose

• Fasting urinary glucose and protein

• Length and weight

- Blood pressure (BP)
- Hemoglobin (Hb) value

Furthermore, we will look at the suitability of the veins for taking blood samples (for using a venflon) and functional ED measurements. After the screening visit, the participant will receive a breakfast.

**4.3 Exclusion criteria**

- Allergic to cow milk or dairy products
- Body mass index (BMI) < 18 or > 25 kg/m2
- Urine glucose concentrations outside normal ranges (>0,25 g/l)
- Fasting blood glucose outside the normal range (3 - 5.5 mmol/L)
- Tobacco smoking
- Taking medication or food supplements.
- Received inoculations within 2 months of starting the study or planned to during the study
- Donated or intended to donate blood from 2 months before the study till two months after the study
- Blood Hb values below 8.4 mmol/L
- Diagnosed with any long-term medical condition (e.g., diabetes, hemophilia, cardiovascular disease, anemia, gastrointestinal disease, renal failure)
- High blood pressure (systolic BP> 140 mmHg and/or diastolic BP>90 mmHg)

**4.4 Sample size calculation**

Based on the methodological paper by de Roos *et al. (2003) 11*we can estimate that we need 7 subjects to obtain a 6 FMD% difference before and after the fat load with 90% power and alpha of 5%, using an within-subjects SD of 2.8 FMD%. Van Oostrom *et al.*(2003) observed a reduction from 13 FMD% to 3 FMD% after a high-fat load in healthy men 4. However, we know that the within-subject coefficient of variation for FMD can be large and that FMD measures differ between studies. 13 The latter may be due to methodological reasons18. Hence we propose to include 20 subjects, which enables us to detect a difference in 3 units of endothelial function as measured with ionthophoresis (paired t-test, SD 4.5 units, power 80%, alpha 5%), which seems plausible 13.

**5. INTERVENTION**

**5.1 Intervention meals**

Each participant will receive a high-fat challenge or a ‘control’ meal. The HF meal will consist of a milkshake, containing a total amount of 95g of fat (consisting of mainly saturated fatty acids) and the total volume that will be consumed is 500ml. The ‘control’ meal will consist of a milkshake of witch the content can be compared to a normal breakfast. Both shakes/meals should be consumed within 10min. Table 1 describes the ingredients, macronutrient composition and total energy intake for each shake/meal.

**Table 1:** *A)**Ingredients used for both milkshakes and B) Nutritional values of the two milkshakes according to Nevo2006.*

A)

| HF milkshake | ‘control’ milkshake |
| --- | --- |
| 53% Whipped cream  3% Sugar  44% Water | 42% full cream milk  47% full cream yoghurt  10% lemonade  1% wheat fiber |

**B)**

|  | HF milkshake (500ml) | ‘control’ milkshake (500ml) |
| --- | --- | --- |
| Energy (KJ) | 3992.08 | 1674.00 |
| Protein (g) | 6.13 | 17.00 |
| Fat (g)  Of which saturated (g) | 94.83  54.22 | 14.50  9.00 |
| Carbohydrates (g) | 22.31 | 49.70 |
| fiber (g) | 0 | 2.30 |

**5.2 Guidelines during the study period**

All participants will be advised to keep the same dietary habits as before the study period. In order to standardize the participants‘ nutritional status before each testing day, the participants will be asked to:

- Consume a low fat evening meal (<10g) the day before each study day (will be provided).
- Not consume any alcohol the day before each study day
- Avoid strenuous exercise the day before each study day
- Fast overnight before each study day (min of 10 hours).

Details on how to live up to these guidelines will be given (and discussed) to each participant before the start of the study.

**6. METHODS**

**6.1 Study outcomes**

***6.1.1 Measurements of primary study outcomes***

Four different non invasive functional measurements will be used to establish a reliable method to measure HF induced ED and to observe the effect of a HF meal on systemic arterial stiffness, local arterial stiffness, macro circulation and micro circulation. The total protocol of the EF measurements will take 1.5 hours (for details see paragraph 6.2.4). Functional measurements will be performed at baseline (T=-1.5) and 3 and 6 hours after the challenge, because previous studies observed a maximal response in macro vascular circulation by FMD after 3 hours that returned to normal after 6 hours4, 9. All functional measurements will be performed on the right side of the body in a climate controlled room.

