**1.2 Functional measures of endothelial function**

EF can be assessed by several methodologies/functional measurements of which each has its own advantages and drawbacks. Currently, HF meal induced ED is only studied on a macro vascular level by using FMD. Flow mediated dilatation is a commonly used technique to investigate the ability of vascular endothelial cells to respond to changes in shear stress. However, this technique is time consuming and large variations in reproducibility are found in the literature (reviewed by De Roos *et al*. 2003 11).

There are other methodologies to monitor EF besides FMD, although these are not applied to monitor HF meal induced ED. Another way to (indirectly) indicate EF on macro vascular level is by measuring the arterial stiffness12. Arterial stiffness (i.e. impairment of the cushioning capacity) leads to an increase in systolic blood pressure and can be estimated by quantifying pulse pressure, but is better described by distensibility and compliance coefficients, pulse wave velocity and wave reflection. It is also possible to monitor EF on a micro vascular level. Abahji *et al.* (2006)13 observed impaired micro vascular EF after acute hyperhomocysteinemia by using ionthophoresis techniques. The question remains if these other methodologies are also applicable to observe a HF meal induced ED.

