**2.1 Research questions and hypothesis**

1. Does a HF meal have an effect on EF that can be measured with several measures of micro- and macro-vascular function and which of these methodologies is best applicable to measure HF meal induced ED?

 *Both micro- and macro-vascular endothelial function will be affected after a HF meal. All used methodologies can therefore be used for measuring HF induced ED, although some might be more applicable (more accurate, easier to use).*

1. Does a HF meal results in changes in PBMC gene expression profiles, white blood cell activation markers, plasma cytokine profiles and other markers of ED and can these observed effects be correlated to the functional measurements of ED?

 *A high fat challenge will have an effect on PBMC gene expression profiles, white blood cell activation, plasma cytokine profiles and other plasma markers of ED. Some of these changes will correlated either positively of negatively to the outcomes of the functional measurements and might be good candidate early biomarkers for ED and will provide us with leads for a possible mechanism.*

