**3. STUDY DESIGN**

**3.1 Intervention study**

This study is a double-blind cross-over intervention (challenge) study, planned to run (incl. a 2 week break during Christmas/ new year) from 20-10-2008 till 15-02-2009. A total of 20 healthy male individuals will receive a) a milkshake containing 95g of fat (high-fat challenge) or b) a milkshake containing the same nutritional and energetic value of an average breakfast (based on ‘voedselconsumentenpeiling’ 2003 from TNO). Data obtained with this ‘control’ milkshake will not directly be compared to the HF milkshake, but will be used to obtain knowledge about normal circadian rhythms in EF. Both interventions will be performed in triplicates, to obtain information on variation in the different measures of EF and the variation in PBMC gene expression, white blood cell activation markers, plasma cytokine profiles and other plasma markers of ED. This means that each individual will visit the department on 6 different days. All testing days will be randomly divided over the study time period, with a minimal period between the testing days of 7 days, in order to exclude carry over effects. Randomization is performed in which only the variants ABABAB and BABABA are possible. Two participants will be evaluated on each testing day (see paragraph 6.2.4)

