**8. STATISTICAL ANALYSIS**

To observe an effect of HF on EF, changes in primary outcome variables will be tested using repeated measures ANOVA (mixed model) using pre-defined contrasts, i.e. 3 versus 0 hrs and 6 versus 3 hrs. ANOVA will also be used to quantify the within- and between subject variation of the various measurements.

Changes in secondary outcome variables will be tested using repeated measures ANOVA (mixed model) using pre-defined contrasts, i.e. 3 versus 0 hrs and 6 versus 3 hrs. Additionally, incremental areas under the curve will be calculated for all significant altered secondary outcome variables using the trapezoïdal rule and compared between meals using one-way ANOVA. All statistical analysis will be performed with SPSS version 15.0.

Data analysis of the microarrays will be performed using a Bayesian linear regression model (implemented in the software package LIMMA; [www.bioconductor.org](http://www.bioconductor.org/)). Raw microarray data will be normalized using RMA quantile normalization. Statistically significant changed genes will be identified by student paired t-test followed by a false discovery rate correction (FDR) The latter is used to correct for multiple testing.

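### Blinding the meal does not protect the primary time contrasts from operator or reader expectation, and no masking to time point at reading is stated

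*Protocol*

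**What the plan says.** - **Blinding.** Section 3.1: "This study is a double-blind cross-over intervention (challenge) study". The label is not explained further. The randomised factor is the meal, given three times each in one of two strictly alternating orders.
- **Role of the control meal.** Section 3.1 says its data "will not directly be compared to the HF milkshake, but will be used to obtain knowledge about normal circadian rhythms in EF".
- **Primary test.** Section 8 tests changes in the primary outcomes by repeated measures ANOVA (mixed model) "using pre-defined contrasts, i.e. 3 versus 0 hrs and 6 versus 3 hrs".
- **Timetable.** Section 6.2.4 and Tables 2 and 4 fix the clock times: a baseline session before the shake, then sessions at 3 h and 6 h. The second participant of the day runs 1.5 hours later.
- **Expected result.** Section 6.1.1 justifies the time points by noting that earlier studies saw "a maximal response in macro vascular circulation by FMD after 3 hours that returned to normal after 6" hours. For the measures as a whole, section 2.1 gives only a general hypothesis: "Both micro- and macro-vascular endothelial function will be affected after a HF meal".
- **Reading.** Sections 6.1.1 and 6.2.4 describe echo-tracking ultrasound, tonometry and laser Doppler. They do not say who evaluates the recordings, whether this is done live or offline, or whether it is masked.

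**The concern.** Blinding protects a comparison only if it hides the factor being compared. Here the hidden factor is the meal and the compared factor is time since the meal. The comparison that meal masking would protect, HF against control, is the one that section 3.1 sets aside.

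A small systematic shift in what is recorded or read at 3 h is bias, not noise. Neither 20 men nor three HF days average it out, and replication makes it easier to declare significant. For FMD, a downward shift at 3 h would look like the expected dysfunction at 3 h with recovery at 6 h. The study is meant to pick a method for later work (sections 1.4 and 9.4.1), so a false signal in one measure could also affect that choice.

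**Working it through.** **1. What the blinding covers and what is tested**

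| Element | What is compared or hidden | Source |
| --- | --- | --- |
| Double-blind label | Meal | Section 3.1 |
| Primary contrasts | Time: 3 v 0 h, 6 v 3 h | Section 8 |
| Direct HF v control comparison | Excluded | Section 3.1 |
| Time point at acquisition | Evident from the timetable | Section 6.2.4, Tables 2 and 4 |
| Time point at reading | Nothing stated | Sections 6.1.1, 6.2.4 |

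**2. The plan's own figures**

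These were checked with an exact paired t-test (noncentral t), two-sided 5%; sidedness is assumed.
- Iontophoresis: difference 3 units, SD of the difference 4.5, 80% power gives n = 20 (power at 20 is 80.7%).
- FMD: difference 6 FMD%, within-subject SD 2.8, so SD of a difference = 2.8 × √2 = 3.96. For 90% power n = 7 (power at 7 is 91.3%).

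Both sample sizes in section 4.4 reproduce, so no stated figure is wrong. The FMD inputs are reused below.

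**3. Illustration of a reading shift**

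Inputs from the protocol: n = 20, within-subject SD 2.8 FMD%, three HF days. Assumptions: no true mean change, a systematic shift b at 3 h on every HF day, days independent, two-sided 5%. True responses vary between men with SD s.

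SD of a man's mean 3 v 0 h change over k days = √(2 × 2.8²/k + s²)

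- k = 3: √(5.227 + s²) = 2.29, 3.04, 4.61 for s = 0, 2, 4
- k = 1: √(15.68 + s²) = 3.96, 4.44, 5.63 for s = 0, 2, 4

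Noncentrality = b × √20 / SD. For example, b = 1, k = 3, s = 0 gives 4.472/2.286 = 1.96 on 19 degrees of freedom.

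Probability of a significant 3 v 0 h contrast:

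| Shift b | Days averaged | s = 0 | s = 2 | s = 4 |
| --- | --- | --- | --- | --- |
| 0.5 FMD% | 1 | 8% | 8% | 7% |
| 0.5 FMD% | 3 | 15% | 11% | 7% |
| 1 FMD% | 1 | 19% | 16% | 12% |
| 1 FMD% | 3 | 46% | 29% | 15% |

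A shift of 1 FMD% is one sixth of the 6 FMD% planning difference. A shift confined to 3 h enters the 6 v 3 h contrast with the same size and opposite sign.

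**4. The contrast the plan leaves out**

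If the shift is the same on both meals, HF change minus control change has expectation −b − (−b) = 0. In 20,000 simulated trials (three days per meal, s = 0), its rejection rate was 5.2% for shifts of 0.5 and 1 FMD%, against 16% and 46% for the HF-only contrast in the same runs.

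**The case against.** **The protocol is silent, and silence is not unmasked reading.** This stands. A reader might infer that expectation does enter the primary contrasts. The documents support only that it can: the timetable shows that the person acquiring a recording knows the hour, but masked offline reading is neither described nor excluded.

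**Meal masking dilutes the expectation.** This stands in part. The fall at 3 h is expected after a fat load, and a reader masked to meal does not know whether the day is an HF day. It is therefore too strong to call the contrast fully open-label. A reader who shifted every 3 h value would also leave a trace on control days. The protection is incomplete: the direct comparison is excluded, and with only two alternating orders, learning the meal on one day reveals all six.

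**The expected course is stated for FMD only.** This stands. Section 6.1.1 gives no time course for tonometry, carotid ultrasound or iontophoresis; only the general hypothesis in section 2.1 applies to them.

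**The readouts are largely instrumental.** This narrows the room for subjective reading by an amount the documents do not give. It is tempting to add that bias would favour the more reader-dependent methods. The protocol does not rank the methods in that way, and its remark in section 1.2 that "this technique is time consuming and large variations in reproducibility are found in the literature" concerns variability of FMD, not directional bias.

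**The size is assumed.** This stands. The 46% is the upper corner: the larger shift on every HF day, three days averaged, and no variation in response between men.

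**Conclusion.** The point holds as a gap in protection, not as a demonstrated bias. Meal blinding does not shield the 3 v 0 h and 6 v 3 h contrasts, the one comparison in which a common shift would cancel is excluded, and no masking to time point at reading is stated. The exposure is clearest for FMD and weaker for the other primary measures.

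The size cannot be taken from the documents. For assumed shifts of 0.5 to 1 FMD% the false-positive rate of the 3 v 0 h contrast runs from about 7% to 46%, depending on how many days are averaged and how much men differ in response. It rests on a shift that is present in full on each HF day. If masked offline reading is already intended, saying so closes the reading part of the point. It is a worthwhile, low-cost improvement.

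**What to change.** - **Section 6.1.1.** State that saved recordings are read offline under codes hiding participant, date, clock time and meal. A man's 18 sessions (6 days × 3) are read in random order after his last visit, and values are locked before decoding. Apply this at least to the ultrasound diameter recordings behind FMD, CC, DC and YEM.
- **Section 3.1.** State that blinding covers time point at reading as well as meal.
- **Section 8, alongside the planned contrasts.** Report HF change minus control change for the primary outcomes, with a matching edit to the sentence in section 3.1 that excludes the comparison. This cancels any shift common to both meals, including one made at acquisition, but not a shift that occurs only on days the operator believes to be HF days.

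**Cost.** Raw recordings must be stored, coded and shuffled, and values become available only after a man's last visit. No extra visit or procedure for participants is needed. Acquisition stays unmasked, so the masked reading covers only part of the exposure.

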**Macro vascular regional arterial stiffness by tonometry**

Pressure sensors (applanation tonometers) are applied at the carotid and femoral artery to record pressure waveforms (reviewed by Stehouwer *et al*.19). From these waveforms we can conduct two measurements of arterial stiffness: the pulse wave velocity (pwv) and the augmentation index (AIx).

- The pulse wave velocity (pwv): The speed of the pressure wave travelling along an arterial segment (e.g. carotid-femoral). It is determined by the length of the arterial segment divided by the time it takes for a pressure wave to travel from the carotid artery to the femoral artery. An ECG is necessary as a reference. Greater pwv values indicate greater stiffness.
- Augmentation index (AIx): The supplementary increase in blood pressure during systole, due to the reflection of the forward travelling pressure waves from the peripheral circulation. AIx is an estimate of stiffness and wave reflection and therefore provides indirect information on arterial stiffness.

**Macro vascular local arterial stiffness by ultrasound**

Ultra-sonography (echo tracking) of the carotid arterial wall (reviewed by Stehouwer *et al*.19) provides several estimates:

- Compliance coefficient (CC): Absolute change in lumen area for given increase in pressure.
- Distensibility coefficient (DC): Relative change in lumen area for a given change in pressure
- Young’s elastic modulus (YEM): The pressure step per squared centimeter required for (a theoretical) 100% stretch from resting length, determined by the arterial diameter (D), divided by DC, multiplied by the thickness of the intima-media complex (IMT): YEM = D/DCxIMT.

These estimates are determined directly from simultaneous changes in (local) pulse pressure and arterial diameter or area. The lower the DC or CC and the higher the YEM of an artery the higher is its stiffness. Local arterial stiffness will also be determined for the brachial artery since all above mentioned estimates will also be determined during the measurements for FMD (see below).

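### Young's elastic modulus is printed as D/DC times IMT, which is not a pressure and gives wall thickness the wrong direction; it should read D/(DC x IMT)

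*Protocol*

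**What the plan says.** Protocol section 6.1.1, under local arterial stiffness by ultrasound, lists three estimates from echo tracking: the compliance coefficient (CC), DC and YEM. Four statements there matter.

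- DC is the "Relative change in lumen area for a given change in pressure".
- YEM is described as "The pressure step per squared centimeter required for (a theoretical) 100% stretch from resting length".
- YEM is calculated in words as "determined by the arterial diameter (D), divided by DC", and then "multiplied by the thickness of the intima-media complex (IMT): YEM = D/DCxIMT". No brackets are printed, and no other part of the protocol gives a different form.
- On interpretation: "The lower the DC or CC and the higher the YEM of an artery the higher is its stiffness".

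The estimates apply to the carotid artery, and the section adds that "Local arterial stiffness will also be determined for the brachial artery since all above mentioned estimates will also be determined during the measurements for FMD". Section 6.1.1 covers the primary outcomes. Section 8 tests these by repeated-measures ANOVA with contrasts of 3 against 0 hours and 6 against 3 hours, and also uses ANOVA to estimate variation within and between participants.

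**The concern.** An elastic modulus is a stress per unit strain, so it carries the unit of pressure. For a given diameter and distensibility it must fall as the wall gets thicker, because more material is carrying the same load. The printed expression does neither when read from left to right.

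The formula defines a primary variable in two arteries. Anyone who programmes it from the protocol would obtain a quantity that is not a modulus. Between two participants with equal D and DC, it would label the one with the thicker wall as having the stiffer wall material, when the modulus says the opposite. The study aims to compare methods and carry one forward, so the variable should be defined correctly where the protocol chooses to define it.

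**Working it through.** **Inputs from the protocol (section 6.1.1).** DC = (dA/A)/dP, so its unit is 1/pressure. D and IMT are lengths. YEM is meant to be a stiffness expressed as a pressure for a theoretical 100% stretch.

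**Step 1: units of the two readings.**
- As printed, left to right: (D/DC) x IMT has unit mm / (1/kPa) x mm = kPa mm², which is a force.
- With brackets: D/(DC x IMT) has unit mm / ((1/kPa) x mm) = kPa, which is a pressure.

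**Step 2: thin-wall derivation, small increments.** Wall stress is P x D/(2 x IMT) and strain is dD/D. For small changes dA/A is about 2 dD/D, so DC = 2(dD/D)/dP. Then

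E = [dP x D/(2 x IMT)] / (dD/D) = D/(DC x IMT).

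This is the bracketed form.

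**Step 3: size of the difference.** The ratio of the printed to the bracketed form is IMT², whatever D and DC are. The protocol gives no arterial values, so those below are assumptions for illustration.

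| Assumed inputs | DC (per kPa) | D/(DC x IMT) | (D/DC) x IMT | Ratio |
|---|---|---|---|---|
| Carotid: D 6.5 mm, dD 0.65 mm, pulse pressure 6 kPa, IMT 0.5 mm | 0.0333 | 390 kPa | 97.5 kPa mm² | 0.25 |
| Carotid, same but IMT 0.6 mm | 0.0333 | 325 kPa | 117 kPa mm² | 0.36 |
| Brachial: D 4.0 mm, dD 0.12 mm, pulse pressure 7 kPa, IMT 0.30 mm | 0.00857 | 1556 kPa | 140 kPa mm² | 0.09 |

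Over an assumed IMT range of 0.3 to 0.8 mm, the bracketed value in kPa is 11.1 to 1.6 times the printed value in kPa mm² (1/IMT²). With lengths in cm, the printed value is smaller by a further factor of 100.

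**Step 4: direction of wall thickness.** With D and DC fixed, raising IMT from 0.5 to 0.6 mm moves the bracketed YEM from 390 to 325 (-17%) and the printed one from 97.5 to 117 (+20%). A 10% higher IMT gives 1/1.1 = 0.909 (-9%) against 1.10 (+10%). The reversal does not depend on the assumed values.

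**Step 5: comparisons between people and arteries.** Since IMT² differs from one participant or artery to the next, the printed form is not a simple rescaling. In the table, brachial over carotid YEM (first carotid row) is 1556/390 = 4.0 with brackets and 140/97.5 = 1.4 as printed.

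**Step 6: within-person contrasts.** Printed YEM = bracketed YEM x IMT². If a participant's IMT is constant over the day, IMT² cancels from any ratio of two time points, so the relative change is identical and its direction is preserved. On the raw scale each participant's change is multiplied by his own IMT², so participants are weighted differently. If IMT does move, the forms can part: suppose D rises by 8%, DC is unchanged and D x IMT is conserved. The bracketed form then changes by 1.08² = 1.17 (+17%) and the printed form by 1.08/1.08 = 1.00 (none).

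**Step 7: measurement error in IMT.** On the log scale, IMT enters with coefficient -1 in the bracketed form and +1 in the printed one. Independent error in log IMT therefore adds the same variance to both, to first order.

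**The case against.** The strongest reply is that this is a notation fault. D over (DC x IMT) set as a stacked fraction looks just like the printed line once typed inline without brackets, and describing YEM as a pressure step points to the bracketed meaning. It is fair to allow that brackets were lost. The sentence in words runs in the same order as the symbols, however, and can be read as division by a product only with effort. A reader who follows the text as written gets the wrong quantity.

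Three stronger readings are tempting, and the protocol does not support them.

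- *A reader might infer that the trial's YEM values will be wrong.* That holds only if they are calculated from this line. The section describes estimates that echo tracking provides, and the software may already apply the correct form.
- *A reader might infer that the tests of the meal effect are invalid.* Step 6 shows that relative within-person changes agree where IMT is constant over the day. The protocol does not say whether IMT is measured again at each time point.
- *A reader might infer that the reproducibility comparison between methods is distorted because IMT error enters with the opposite sign.* Step 7 shows that sign does not matter for independent error. A difference would need IMT, or its error, to be correlated with D or DC, and the protocol gives nothing from which to quantify that.

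Reach is also limited. CC and DC describe the same local stiffness without this formula, and pulse wave velocity, augmentation index, FMD and iontophoresis do not use it. The sample size in section 4.4 rests on FMD and iontophoresis and is untouched.

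**Conclusion.** The formula is wrong as written and should be corrected. By the protocol's own definition of DC, the printed expression is a pressure times length squared and rises with wall thickness at fixed D and DC; D/(DC x IMT) is the form that is a pressure.

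If carotid and brachial YEM were computed as printed, they would be wrong in absolute value, units and between-participant spread, because the forms differ by IMT² (0.25 and 0.09 in the assumed carotid and brachial examples, with lengths in mm). The units argument needs no assumption beyond the protocol's definition of DC. The role of wall thickness follows from standard thin-wall mechanics. Only the numerical examples rest on assumed arterial values.

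The consequence is confined to YEM and depends on the printed form actually being used. The description of YEM as a pressure step per unit area is a related slip: pressure per cm² is not a pressure and matches neither reading.

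**What to change.** In section 6.1.1:

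1. Write YEM = D/(DC x IMT), in kPa.
2. Reword the sentence so that D is divided by the product of DC and IMT.
3. Replace the phrase about a pressure step per squared centimetre with a description of YEM as the stress (a pressure) for a theoretical 100% stretch.
4. Confirm that the calculation code or the echo-tracking export uses this form for both the carotid and the brachial artery.

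The cost is one formula, one sentence and one check of the calculation. Design, sample size and measurements do not change. If values have already been produced with the printed form, dividing each by the square of the IMT used for it, in the same length unit, recovers the correct YEM.
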